#### Assessment of depression relapse

Patients will receive a text message once every 2 weeks (except at 3 and 6 months post-ECT; when they are invited for a more thorough interview at the hospital) to enquire whether they experienced either core symptom of depression over the past 2 weeks: 1) Have you been consistently depressed or down, most of the day, nearly every day, for the past 2 weeks?; 2) In the past 2 weeks, have you been much less interested in most things or much less able to enjoy the things you used to enjoy most of the time? . Answer can be yes or no. The text messages will be sent using SurveySignal at 18.00 h containing a link to a two question LimeSurvey questionnaire. If the patient does not respond within the first hour, a reminder text message will be sent. If the patient either does not respond to the screening questions within a 24-h timeframe, or answers either of the questions affirmatively, the patient will be called by the researcher to conduct the semi-structured Mini International Neuropsychiatric Interview (MINI v7.0.0) depressive episode module (A). If a relapse has concluded, patients will be referred for psychiatric assessment to their treating psychiatrist for adequate clinical care. These phone calls will be recorded and stored for later evaluative purposes and diagnosis by an independent rater.

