## Background

Virtually all national and international guidelines consider electroconvulsive therapy (ECT) a valuable, effective, safe and tolerable therapeutic option in cases of treatment resistant major depressive episode (MDE) and for severe and life-threatening depressive conditions (i.e., psychotic depression, high suicide risk, life threatening malnourishment) [1, 2]. During the ECT procedure, performed under general anesthesia and a muscle relaxant to minimize side effects, epileptic activity is induced/generated by a controlled passage of electric current through the brain. Even though the exact neurobiological mechanism of action remains largely unclear, antidepressant effects are attributed to changes in neurotransmitter levels, improved neuroplasticity, increased functional connectivity, and an increase in plasmatic brain-derived neurotrophic factor (BDNF). The therapeutic efficacy of ECT for MDE is characterized by a fast onset of action and high initial response rates. Meta-analyses support superiority over pharmacotherapy [3] and response rates of 74,2% for MDE in unipolar patients and 77,1% for MDE in bipolar patients are reported [4]. The pooled remission rates, even in cases of treatment resistance, are 52,3% for unipolar and bipolar patients [4].

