### Procedure

Outcome assessors and/or ECT-physicians will provide adequate verbal and written information regarding the study to all eligible patients at the ECT-clinic. Researchers will obtain written informed consent from all patients willing to participate and able to give consent. After consenting to participate and before the start of ECT treatment, all patients will complete baseline cognitive function assessment (CANTAB, PASAT), cognitive complaints (SSMQ), depressive symptomatology (BDI-II, HAM-D), depressive status (RDQ), rumination (RRS-10) and quality of life (QLDS). After ECT completion, cognitive functioning (CANTAB, PASAT), cognitive complaints (SSMQ), depressive symptomatology (BDI-II, HAM-D), depressive status (RDQ), rumination (RRS-10) and quality of life (QLDS) will be assessed. Moreover, all patients will receive standard clinical care. Patients will receive standard pharmacological relapse prevention, under the responsibility of their treating physician, started during (nortriptyline) or after (lithium) ECT by combining nortriptyline (50-150 ng/ml) and lithium (≥0.5 mmol/l) for MDD and lithium (≥ 0.5 mmol/l) alone for BDD. In case of contra-indication for nortriptyline and/or lithium, alternative relapse prevention options will be explored by the treating physician. As is standard clinical care, monthly lithium dosing and testing of renal and thyroid function will be performed by the treating physician. If renal function deteriorates during follow-up this should be reported as an adverse event and may necessitate lithium discontinuation. Before dismissal from the ward participants will receive a two-session CBT-based relapse prevention group therapy and individual counseling by a social worker. Only patients who achieve a 25% or more reduction in BDI-II or HAM-D scores [36] will be randomly assigned to one of two conditions (CCT or active control), see Fig. 1 as cognitive control training has evidence as a relapse prevention strategy and not as a treatment for MDE. Non-responders to ECT will be excluded to allow further clinical treatment for MDE outside of this study protocol. After completion of the CCT, relapse of depression will be monitored for a period of 6 months using mobile assessments of depression (every 2 weeks) and telephone interviews in case of possible relapse. If there is an indication of relapse, patients will be assessed by the semi-structured Mini International Neuropsychiatric Interview (MINI v7.0.0) depressive episode module (A) and referred for psychiatric assessment to their treating psychiatrist for adequate clinical care if necessary. Patients who relapse will be excluded only if they receive a subsequent ECT-course as this might affect cognitive parameters. At three and 6 months, a more extensive evaluation will be performed investigating cognitive parameters (SSMQ), depressive symptomatology (BDI-II, HAM-D), depressive status (RDQ), rumination (RRS10) and quality of life (QLDS). We refer to Fig. 2 for an overview of the study design and Table 1 for the trial registration data set.

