#### Adverse events

At each control visit, adverse events will be routinely screened for by asking a non-leading question to the patient such as: ‘Have you had any health problems since your last visit?’. In case of an emergency, the principal investigator will be contacted. Serious adverse events occurring during the clinical trial must be reported within 24 h to the principal investigator. If the principal investigator is not available, patients are referred to the on-call psychiatrist at the Ghent University Hospital. All participants are insured through a no-fault insurance policy conform Belgian law for human experiments. Insurance information and all contact details are provided in the informed consent document.

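### Relapse is diagnosed by a telephone MINI, with no rule for patients who cannot be interviewed; with LOCF and an exclusion after new ECT, some of the worst outcomes can be lost or carried forward as relapse-free

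*Protocol article*

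**What the plan says.** Relapse matters to this trial. The Sample size calculation section names it among the primary outcome measures and takes N = 88 from a chi-square test on it, although Table 1 lists time to relapse as secondary.

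The Assessment of depression relapse section describes a fortnightly two-question text message. The trigger for the next step is: "If the patient either does not respond to the screening questions within a 24-h timeframe, or answers either of the questions affirmatively". Then "the patient will be called by the researcher to conduct the semi-structured Mini International Neuropsychiatric Interview (MINI v7.0.0) depressive episode module (A"). The material for independent judgement is the call itself: "These phone calls will be recorded and stored for later evaluative purposes and diagnosis by an independent rater". The Procedure section gives the same route: "If there is an indication of relapse, patients will be assessed by the semi-structured Mini International Neuropsychiatric Interview (MINI v7.0.0) depressive episode module (A"). At 3 and 6 months the text is replaced by a visit, "when they are invited for a more thorough interview at the hospital".

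On repeat ECT, the Procedure section says: "Patients who relapse will be excluded only if they receive a subsequent ECT-course as this might affect cognitive parameters".

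The Data management and analyses section plans intention to treat for the main analyses. LOCF is to handle data missing through non-response, drop-out or relapse. Relapse is compared by a Pearson chi-square test, and time to relapse by Kaplan-Meier curves and a log-rank test. No censoring rule is stated.

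Serious events have a reporting line ("Serious adverse events occurring during the clinical trial must be reported within 24 h to the principal investigator"), but the article does not connect it to the relapse endpoint.

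**The concern.** The Background lists among the indications for ECT "severe and life-threatening depressive conditions (i.e., psychotic depression, high suicide risk, life threatening malnourishment"), and the Procedure section itself foresees repeat ECT during follow-up. Suicide, acute admission and a new ECT course are therefore foreseeable in this population, and they are among the most serious ways in which relapse prevention can fail.

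An endpoint that depends on an interview captures relapses mild enough to be interviewed. A patient who has died, or who is never well enough for the call, produces no MINI and no recording for the independent rater. If the gap is filled by the last known status, that status is relapse-free. If the patient is removed after new ECT, an event may leave the comparison altogether. Either way the relapse rate is understated, and the events lost are not a random sample of relapses.

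**Working it through.** **1. Follow each type of patient through the text.**

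- *Suicide after negative screens.* There is no MINI and no later visit. The article does not name suicide as a relapse event. LOCF is promised for missing outcome data and relapse status is not exempted, so the last status (no relapse) can be carried into the chi-square test. In the Kaplan-Meier analysis the patient might instead be censored at last contact. The article does not say so; if it were done, the censoring would be informative.
- *Psychiatric admission, never interviewed.* The same applies. An unanswered text leads to a call, not to a relapse-free score, and an inpatient may still be interviewed then or later. The gap concerns only patients who are never reached.
- *New ECT course after relapse.* The Procedure section treats the patient as already relapsed and then excludes them. It does not say whether the event is kept and only later cognitive data are dropped, or whether the patient leaves all analyses. The second reading contradicts intention to treat.

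**2. Reproduce the article's figure.** Inputs from the Sample size calculation section: w = 0.3, α = 0.05, power 0.80.

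N = (z₀.₉₇₅ + z₀.₈₀)² / w² = (1.960 + 0.842)² / 0.09 = 87.2, rounded up to 88. The stated 88 reproduces (power 0.804).

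**3. Expected relapses.** Inputs: control rate 37.7% (Background), odds ratio 0.38 (Sample size calculation), 44 per arm (equal arms assumed).

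- Control odds: 0.377 / 0.623 = 0.605.
- CCT odds: 0.38 × 0.605 = 0.230, so the CCT rate is 0.230 / 1.230 = 18.7%.
- Expected relapses: 44 × (0.377 + 0.187) = 24.8, so one lost event is 1 / 24.8 = 4.0%.
- With no effect: 88 × 0.377 = 33.2, so one lost event is 1 / 33.2 = 3.0%.

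**4. How much one event can matter.** An illustrative result near expectation is 17/44 against 8/44: chi-square = 88 × (17×36 − 8×27)² / (44 × 44 × 25 × 63) = 4.53, p = 0.033. With one control event lost, 16/44 against 8/44 gives 88 × (16×36 − 8×28)² / (44 × 44 × 24 × 64) = 3.67, p = 0.056.

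**5. Range under assumed loss.** Let a share m of true relapses be scored relapse-free, equally in both arms. The observed rates are then 0.377(1 − m) and 0.187(1 − m).

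| m (assumed) | Difference, points | Power, 44 per arm |
|---|---|---|
| 0% | 19.0 | 0.51 |
| 5% | 18.1 | 0.48 |
| 10% | 17.1 | 0.45 |
| 20% | 15.2 | 0.40 |
| 30% | 13.3 | 0.35 |

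Power starts at 0.51, not 0.80, because these two rates correspond to w = 0.21, not 0.3. That is a separate matter.

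If the lost patients are excluded instead, the observed rate is p(1 − m) / (1 − pm). At m = 10% this gives 35.3% against 17.1%.

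**The case against.** The strongest defence is that the article describes how relapse is screened and diagnosed without claiming an exclusive definition. Several points in it stand.

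- A reader might infer that relapse counts only through a completed MINI. The text never says so. The BDI-II is also to monitor possible relapse (without a cut-off), there are hospital interviews at 3 and 6 months, and a final assessment is planned, where possible, for patients who do not adhere or are not retained. None of these reaches a patient who has died or cannot attend.
- A reader might infer that a new ECT course is scored as no relapse. The Procedure section says otherwise: it presupposes relapse and excludes the patient. The defect there is the exclusion, not a relapse-free score.
- A reader might infer that readmission is always missed, or that the log-rank test is bound to treat these events as non-informative censoring. Readmitted patients may be interviewed, and no censoring rule is stated.
- An article condenses a fuller protocol, so the lack of an event list or censoring rule would be weak grounds on its own. The point rests instead on what is written: an interview-based diagnosis, LOCF under intention to treat, and an exclusion after new ECT. These do not fit together.
- The number of lost events is unknown, and a small equal loss costs little: at 5 to 10%, power falls from 0.51 to between 0.48 and 0.45. Participants and outcome assessors are to be blinded, and the documents give no specific reason to expect loss in one arm only. No claim of bias towards CCT is made here.

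**Conclusion.** The point holds in a limited form. Followed as written, the plan can carry forward as relapse-free a patient who dies by suicide, or who is admitted and never interviewed, after negative screens. It also excludes relapsed patients given new ECT without saying that their event is kept, against its own intention-to-treat statement. The article does not say that such outcomes are non-relapses; it leaves their classification open while fixing a missing-data rule that can resolve it the wrong way.

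Each lost event is about 4% of some 25 expected relapses, or about 3% of 33 if there is no effect. This rests on the 37.7% control rate, the odds ratio of 0.38 and equal arms. How many events would be lost is not known, so the power figures are illustrations only. The change is worth making because relapse sized the trial, the expected count is small, and the correction is cheap.

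**What to change.** For the relapse analyses:

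1. Count as relapse the first of: a MINI-confirmed depressive episode, psychiatric admission for depression, start of a new ECT course for depression, or suicide or suicide attempt. Date it at that event.
2. Have these events classified blind to arm, from serious adverse event reports and other available records, and link those reports to the relapse dataset.
3. State that LOCF is not applied to relapse status.
4. Keep the relapse event of every patient given new ECT, and drop only their later cognitive data if needed. The Procedure section and the intention-to-treat statement must be reconciled on this.
5. Report MINI-only relapse as a sensitivity analysis.

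The cost is endpoint wording, a data link and a modest blinded classification task; serious adverse event reports are already to be collected. Records beyond those reports may take some extra effort to obtain. The downside is that admission and new ECT depend partly on physician judgement; the MINI-only analysis shows whether the result rests on them.

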### Data management and analyses

Participant files, including informed consent forms, will be stored in a locked cabinet with restricted access for a period of 20 years after study completion.

We will use a 4 (time: T2, T3, T4, T5) by 2 (condition: active placebo CCT; real CTT) repeated measures design. The significance level will be set at α = .05.

For our main analyses, we will rely on intention-to-treat analysis (ITT) to model effects of CCT on the outcome measures of interest, using the Last-Observation-Carried-Forward (LOCF) method to handle missing data (due to non-response, drop-out or relapse of depression). Where adequate, effects of CCT on our cognitive measures and questionnaire data will be modeled using repeated measures Analysis of Variance (ANOVA) or Covariance (ANCOVA). Significant interaction effects will be further explored using independent and paired samples *t*-tests. Effects of CCT on relapse of depression will be modeled using a Pearson Chi-Square test. In addition, we will conduct survival analyses (Kaplan Meier estimator) to model time to relapse, using the log-rank test to compare the obtained survival curves.

Qualitative data analyses methods will be used to analyze the interviews regarding satisfaction, acceptability, and appropriateness of the design.

Exploratory analyses will be used to investigate the facial video footage data collected during the ten sessions of CCT or active placebo. From the footage, we will deduce facial landmarks and reactions during the performance of the training as an indication of frustration, engagement and general mood, whereas different factors could be of influence on the effectivity of the training. More specifically, we expect to see differences in, e.g., general facial valence, facial muscle tension and frustration.

## Discussion

The focus of this study is to investigate cognitive control training as a novel relapse prevention strategy after response to ECT treatment and increasing acceptability of ECT by reducing cognitive side-effects. Cognitive impairment is an important symptom cluster in affective disorders and may continue to affect functional outcomes in a negative matter even after achieving remission of mood symptoms [9]. Cognitive side-effects after ECT are reported by patients as the most disturbing due to their negative impact on quality of life [11]. To date there is only one RCT targeting cognitive-side-effects after ECT by training specific cognitive functions. Choi et al. (2017) conducted a double-blind study investigating the efficacy of a specific memory training targeting anterograde and retrograde memory reporting negative findings [50]. They attributed their null findings in part due to the progression of ECT techniques, such as ultra-brief pulse width and right unilateral (RUL) electrode placement, with a more favorable side-effect profile regarding cognition. In our study patients will receive RUL ECT as this is standard clinical practice at our service. Electrode placement might be switched to bitemporal (BT) stimulation depending on the clinician’s decision if there is no response to treatment. Our sample will thus contain both patients who received RUL and BT ECT. We expect patients treated with BT ECT to experience more cognitive side-effects compared to RUL-ECT treated patients. Even more important, CCT training has a different target, training cognitive control or working memory versus recovering episodic memories and memory skills training. Training cognitive control has shown robust results in patients with depressive episodes as an add-on preventive and/or curative intervention in the treatment of depression.

High relapse rates continue to be a clinical challenge in patients with major depressive episodes and more specifically in those patients treated with ECT due to the treatment resistant and severe nature of their condition. There is an urgent need for novel relapse prevention strategies. Cognitive control training has demonstrated promising results in diminishing relapse rates in patients with depressive symptoms. Reducing relapse and improving acceptability of ECT through reduction of cognitive side effects would be highly desirable outcomes.

## Data Availability

All investigators will have access to the password protected data sets. The datasets generated and/or analyzed during the current study are not publicly available due to confidentiality issues but are available from the corresponding author upon reasonable request.

## Abbreviations

aPASAT: Adaptive Paced Auditory Serial Addition Task
BDD: Bipolar depression
BDI-II: Beck depression Inventory, 2nd edition
BT: Bitemporal
CANTAB®: Cambridge Neuropsychological Test Automated Battery
CCT: Cognitive control training
c-ECT: Continuation electroconvulsive therapy
DSM-5: Diagnostic and Statistical Manual
ECT: Electroconvulsive therapy
HAM-D: Hamilton Depression Rating Scale
MDD: Major depressive disorder
MDE: Major depressive episode
MINI: Mini International Neuropsychiatric Interview
RCT: Randomized controlled trial
MMSE: Mini mental state examination
MOCA: Montreal Cognitive Assessment
RDQ: Remission from Depression Questionnaire
RUL: Right unilateral
RRS-10: Rumination Response Scale 10-items
SSMQ: Squire subjective memory questionnaire
QLDS: Quality of life in Depression Scale
